## Abstract

**Background:**

Orofacial cleft, one of the most common congenital deformities, presents with a plethora of defects, subjecting the patient to a multitude of treatments from a young age. Among the oral hard tissue problems, absence of a maxillary permanent tooth in the cleft region either due to congenital absence or extraction due to compromised prognosis is a common finding. Conventionally, the missing tooth is replaced using a removable or fixed partial denture; however, the treatment modality does not satisfactorily meet patient expectations. The most recent decade has seen increasing use of dental implants in the cleft region; however, the outcome of an immediately loaded dental implant is still elusive for orofacial cleft patients.

**Objective:**

This protocol is for a single-arm clinical trial aimed at determining the treatment outcome of immediately loaded dental implants in patients with a nonsyndromic orofacial cleft.

**Methods:**

Patients meeting the set criteria will be sequentially enrolled until a sample size of 30 dental implants is met and will undergo the proposed treatment according to the predecided protocol. All patients will be followed up at the designated time intervals to record various clinical and radiographic parameters. Implant success will be defined based on the criteria elucidated by Misch et al in the Pisa, Italy Consensus. A quality-of-life assessment questionnaire will also be recorded at the end of patient’s follow-up to determine their acceptance of the treatment.

**Results:**

A total of 30 dental implants will be placed in patients with a nonsyndromic orofacial cleft. Obtained results will be statistically analyzed to determine the treatment outcomes and success.

**Conclusions:**

This study will help determine the feasibility of immediately loaded dental implants in compromised bone sites such as those presented in cleft patients and will help in generating findings that can be used to fill the lacunae currently present in the holistic treatment of cleft patients.

**Trial Registration:**

Clinical Trial Registry of India CTRI/2020/09/027997; http://ctri.nic.in/Clinicaltrials/showallp.php?mid1=47659&EncHid=&userName=dental%20implants

**International Registered Report Identifier (IRRID):**

PRR1-10.2196/25244

## Introduction

### Background

Orofacial cleft is the most common congenital anomaly, with an incidence of 1 in 700 to 1 in 1000 live births across different populations [1]. India reports around 28,600 cleft cases every year with a prevalence of 1.09 in 1000 live births [2]. Cleft can be unilateral or bilateral, occurring either alone or a combination of lip and palate, with or without the involvement of the alveolar process. Complete clefting of the lip that involves the full height is often associated with cleft of the alveolus. In addition to compromised aesthetics and disoriented attachment of musculature leading to compromised functionality, these patients also suffer from various dental anomalies [3]. Tooth agenesis affecting the maxillary lateral incisor in the cleft region is the most commonly found anomaly followed by crowding and delayed development [4,5]. All of these defects in cumulation compromise the patient’s quality of life, and each case poses a challenge for the multidisciplinary health care team due to the unique presentation.

Prosthetic rehabilitation plays a triple role of improving aesthetics, phonetics, and functionality of the patient [6]. Use of dental implants has increasingly become popular, as they help in maintaining the bone dimensions in the reconstructed region along with provision of improved aesthetics compared to conventional replacement options. Dental implant can be opted for only when the patient has reached skeletal maturity so as to avoid potential growth hindrance. Postinsertion, an implant requires a healing period of 3-6 months to firmly integrate with the underlying bone, which is then adequately loaded with a prosthesis. Considering the long treatment duration and compromised aesthetics already incurred by the patient, it is necessary to develop protocols that help reduce the rehabilitation time. Immediate implant loading is one such measure wherein acceptable initial implant stability enables implant loading in as little time as 1 week. This would not only decrease time lapse in 2 consecutive rehabilitative procedures but also help improve the patient’s psychological acceptance. Most studies presented have performed implant loading after the universally followed protocol of 6 months [7], while a few studies have also demonstrated loading after 3 months [8]. Only 1 study has been conducted so far that presented the results of immediate or early implant loading, but it was a retrospective analysis [8,9].

### Aim

The aim of this study is to evaluate the clinical and radiographic success of immediately loaded dental implants in patients with an orofacial cleft.

### Objectives

The objectives of the study are to evaluate the placed single dental implant in the cleft region for clinical and radiological parameters 3 months after dental implant placement; evaluate the placed single dental implant in the cleft region for clinical and radiological parameters 9 months after dental implant placement (6 months after definitive prosthesis); and evaluate and compare the placed single dental implant in the cleft region for clinical and radiological parameters 3 months and 9 months after dental implant placement.

## Methods

A single arm, prospective clinical trial evaluating the clinical and radiological success of immediately loaded dental implants in orofacial cleft patients will be conducted at the GSR Institute of CranioMaxillofacial & Facial Plastic Surgery, Hyderabad, Telangana, India. Ethical clearance for the clinical trial has been obtained from the Institutional Ethical Committees of the associated institutes. A summary of the methodology is presented in Figure 1.

**Figure 1 figure1:**
[figure not shown]
Summary of the research methodology. CBCT: cone beam computed tomography; IOPAR: intraoral periapical radiograph; ISQ: implant stability quotient; OHI-S: Oral Hygiene Index – Simplified; OPG: orthopantogram; QoL: quality of life; SABG: secondary alveolar bone grafting.

### Sample Size Calculation

A recent study showed a success rate of 95% for dental implant–based treatment in cleft patients [10]. With a type I error of 5%, confidence interval of 95%, and 8% margin of error, a sample size of 28 dental implants was obtained. Considering 5% loss to follow-up, an additional 2 dental implants will be placed. Thus, a total sample size of 30 dental implants in sequential patients will be considered for the proposed study.

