## Results

IBM SPSS version 23 and R 4.0.3 will be used for statistical analysis. Results will be aimed at determining the clinical and radiographic success of dental implants in patients with a nonsyndromic alveolar cleft. The Cox model of analysis will be used to determine the shared frailty of dental implants in case of bilateral cleft cases. The Kolmogrov-Smirnov test will be applied to determine the normality of the data. Depending on the data distribution, *t* tests, Wilcoxon tests, and chi-square tests will be utilized to determine statistical significance of clinical and radiological parameters assessed at 3 months and 9 months post implant placement. Binary logistic analysis will be done to compute the predictors of the outcome. CBCTs recorded after dental implant placement will be quantitatively compared to determine the presence of any significant variation in the marginal bone levels. Qualitative assessments of the radiographs will be done to determine the presence of periapical pathology and any other abnormal radiographic findings. Intra- and inter-observer variability in radiographic assessments will be evaluated by using the Kappa statistic. Statistical significance will be set at *P*<.05.

Implant success will be defined based on the guidelines given by Misch et al [19] in the Pisa, Italy Consensus and as presented in the patient record sheet. Statistical comments on the implant survival rate will be given by calculation of a life table analysis.

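### The 8% margin of error for 28 implants rests on a normal approximation that fails at 95% success; a valid interval reaches about 14–15 points below the estimate

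*Protocol article*

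**What the plan says.** The basis for the sample size is in the protocol article under Sample Size Calculation. The planning value is "A recent study showed a success rate of 95% for dental implant–based treatment in cleft patients". The precision inputs follow: "With a type I error of 5%, confidence interval of 95" per cent, then "8% margin of error, a sample size of 28 dental implants was obtained". The allowance for attrition is "Considering 5% loss to follow-up, an additional 2 dental implants will be placed", which leads to "a total sample size of 30 dental implants in sequential patients will be considered". The section names no formula and no interval method.

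Under Methods the design is "A single arm, prospective clinical trial evaluating the clinical and radiological success of immediately loaded dental implants". There is no comparator, no success threshold and no power statement, so the 8% margin is the only quantitative property offered in support of 30 implants. The Limitations section says in general terms that the sample is small and that larger studies will be needed. It does not qualify the 8%.

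**The concern.** A margin of error of 8% around 95% suggests that, if the trial turns out as expected, success rates below about 87% (95 − 8) would be ruled out. That cannot be taken for granted with 28 to 30 binary outcomes and a proportion close to 1. The sampling distribution is then strongly skewed, the symmetric interval runs past 100%, and the true uncertainty lies mostly below the estimate.

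The lower side is the one that matters here. The article presents the trial as evidence on feasibility in compromised bone, with a view to bringing immediate loading into regular practice. If the 8% is carried into the report, or if a symmetric interval is reported to match it, readers will believe that a poor success rate has been excluded more firmly than the data allow.

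**Working it through.** **Inputs** (all from Sample Size Calculation): p = 0.95; 95% two-sided confidence, z = 1.96; margin d = 0.08, read as an absolute half-width; n = 28 evaluable, 30 after 5% loss. Implants are treated as independent.

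**1. Reproducing the plan's figure.** The Wald precision formula is n = z²p(1 − p)/d² = 1.96² × 0.95 × 0.05 / 0.08² = 28.51. The half-width z√(p(1 − p)/n) is 1.96 × √(0.0475/28) = 8.07 points at 28 implants and 7.80 points at 30. For attrition, 28/0.95 = 29.5, so 30. The plan's figures therefore reproduce. The variants tried do not give 28: z = 2 gives 29.7, and a one-sided z of 1.645 gives 20.1. The symmetric Wald reading is thus an inference, but it is the reading that fits.

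**2. Is the approximation usable here?**
- Expected failures: 28 × 0.05 = 1.4.
- Planned upper limit: 95 + 8 = 103%.
- Chance that all 28 succeed: 0.95²⁸ = 0.238. The estimated variance is then zero and the Wald interval has no width.
- Coverage at p = 0.95, by adding binomial probabilities: the Wald interval contains 95% only when 23 to 27 of 28 succeed, so coverage is 0.009 + 0.037 + 0.114 + 0.249 + 0.350 = 0.760 (sum of unrounded terms). At n = 30 it is 0.782. The nominal level is 0.95.

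**3. What valid intervals give.** Exact limits are beta quantiles: the lower limit is the 2.5% point of Beta(x, n − x + 1), the upper limit the 97.5% point of Beta(x + 1, n − x). When all succeed, the lower limit is 0.025^(1/n). The Wilson interval is centred at (p̂ + z²/2n)/(1 + z²/n), with half-width z/(1 + z²/n) × √(p̂(1 − p̂)/n + z²/4n²).

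| Result | Exact 95% interval | Points below estimate, exact | Points below estimate, Wilson |
|---|---|---|---|
| 26/28 | 76.5% to 99.1% | 16.4 | 15.5 |
| 27/28 | 81.7% to 99.9% | 14.8 | 14.1 |
| 28/28 | 87.7% to 100% | 12.3 | 12.1 |
| 29/30 | 82.8% to 99.9% | 13.9 | 13.3 |
| 30/30 | 88.4% to 100% | 11.6 | 11.4 |

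**4. Averages over the binomial distribution at n = 28, p = 0.95.**

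| Method | Mean lower arm | Mean half-width |
|---|---|---|
| Wilson | 14.4 points | 9.0 points |
| Exact | 15.1 points | 9.7 points |
| Jeffreys | 12.2 points | 8.0 points |

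At n = 30 the same averaging gives mean lower arms of 13.7 (Wilson) and 14.3 (exact). For comparison only, a lower arm of 8 points at exactly 95% observed success would need about 68 (Wilson) to 71 (exact) evaluable implants.

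**The case against.** The strongest reply is that the comparison is not like for like. A margin of error is a half-width, and the average half-width is only 9.0 to 9.7 points at 28 implants by Wilson or exact methods, and about 8.0 by Jeffreys. On that measure the stated 8% is short by one to two points at most. This stands: the upper arm averages under 5 points and the shortfall is mainly on the lower side. But the symmetric 8 points implies a lower limit that no method tried delivers on average, and the lower limit is what a reader will use.

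A second reply is that the 14 to 15 points is no fixed quantity. That also stands. It depends on the method (about 12 on average by Jeffreys) and on the observed count (about 12 with no failures and about 16 at 26/28, by Wilson or exact). It should be quoted with its method.

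A reader might infer three stronger things that the document does not support:

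- **That the sample size is miscalculated because 28.51 should round up to 29.** At 28 the Wald half-width is 8.07 points, which is 8% at the precision stated, and the planned 30 give 7.80. This is rounding.
- **That the analysis is deficient because no interval for success is named.** The Results section does say "Statistical comments on the implant survival rate will be given by calculation of a life table analysis", but a survival summary does not contradict an interval for success, and an article may leave the choice of interval to the full plan.
- **That the trial will report a Wald interval.** Nothing says so. The 76% coverage describes the method behind the planning figure, not a specified analysis.

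The Limitations section concedes a small sample, but a general caveat does not correct a specific figure.

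**Conclusion.** The point holds in a bounded form. The 8% is reproduced by a formula that is not valid at about 1.4 expected failures, and it understates the uncertainty below the estimate by nearly half: about 14 to 15 points on average at 28 implants by Wilson or exact methods, against 8. By Jeffreys the figure is about 12, still well above 8. At 29/30, a favourable result for the full planned sample, success of about 83% would remain compatible with the data.

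The conclusion assumes a true success rate of 95%, a two-sided 95% interval, a margin read as an absolute half-width, and independent implants. Any correlation between two implants in a bilateral case is not reflected in these figures. The result shows that the stated precision is wrong. It does not show that 30 implants is too few, since the trial has no threshold or decision rule that the wider interval would fail.

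**What to change.** Keep 30 implants. In Sample Size Calculation, replace the 8% margin with the precision of a valid interval, for example: *With 28 to 30 evaluable implants and about 95% success, a Wilson or Clopper-Pearson 95% interval extends about 14 to 15 points below the estimate (27/28: 81.7% to 99.9%, exact).* When results are reported, give the 9-month success proportion with the same type of interval, not a Wald interval.

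This costs a change of wording. It adds no implants, visits or data collection. The stated precision becomes less favourable.

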### Patient Selection

Without gender bias, consecutive patients meeting the inclusion and exclusion criteria will be recruited until a sample size of 30 dental implants is met. Signed informed consent to be part of the study will be obtained from the patient or their parent or guardian. Owing to the global COVID-19 pandemic, thorough COVID-19 history and consent will also be obtained. Institutional COVID-19 standard operating procedures will always be strictly followed. Before the beginning of treatment, each patient will be allotted a unique identification number to be used to designate them henceforth. Complete patient records including intra- and extra-oral photographs of the patients at all stages will be maintained, while maintaining confidentiality.

### Inclusion Criteria

To be included in the study, patients will need to be older than 16 years, have an asyndromic orofacial cleft, have a unilateral or bilateral cleft alveolus, have undergone secondary alveolar bone grafting (SABG) between 9 and 12 years of age, require single tooth replacement of the lateral incisor/canine region only on the affected cleft side, not have any systemic diseases, and have no symptoms of COVID-19 or tested negative for SARS-CoV-19 virus.

### Exclusion Criteria

Patients will be excluded when they are not willing to participate and follow-up for the prescribed study duration, have a syndromic cleft, do not require tertiary bone grafting, are unable to maintain oral hygiene (patients with a lack of manual dexterity or any kind of hand skeletal deformity), and have a history of bruxism and/or smoking.

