### Operative Assessment

All patients with a single tooth missing in the cleft area will undergo preoperative screening using an orthopantogram (OPG) supplemented with an intraoral periapical radiograph (IOPAR) and bone mapping to determine the need for tertiary grafting. Prior to tertiary grafting, all patients will have the Oral Hygiene Index-Simplified (OHI-S) recorded followed by conduction of oral prophylaxis [11]. Following standard procedure guidelines, bone grafting will be done by a single operator using either an autologous symphyseal bone graft or iliac bone graft, depending on the amount of bone required [12-14]. Before proceeding with implant surgery, the OHI-S will be re-assessed and compared with the previously recorded observations. This will help to determine the patients’ attitudes towards oral health and their motivation towards maintaining oral hygiene. Cone beam computed tomography (CBCT) will be recorded 3-6 months after grafting to evaluate the integration of the grafted bone and plan implant placement. Before proceeding with implant surgery, the OHI-S will be re-assessed and compared with the previously recorded observations. In all patients, titanium dental implants (TitanGrade 4, blasted etched implant surface, Bredent GmbH Co, Senden, Germany) will be placed following a one-stage protocol. Additional bone graft material will be used to ensure complete bony coverage of the dental implant surface, if required. The implants will be placed slightly subcrestally, and the primary implant stability will be clinically evaluated by measuring implant stability quotient (ISQ) values using a Penguin^RFA^ device. The obtained values will be interpreted as follows [15]: ISQ ≥70: high initial stability and suitable for immediate loading; ISQ 55-70: moderate stability; ISQ ≤55: low/questionable stability and not suitable for immediate loading. Following the immediate loading protocol, all implants will be loaded with a provisional prosthesis made of autopolymerizing resin (ie, a provisional prosthesis will be placed within 7 days of dental implant placement) [16]. All patients will be educated about oral hygiene habits to ensure proper care of the placed implant and prosthesis along with use of a 0.12% chlorhexidine rinse for 30 seconds at least twice a day [17].

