### Scope

This study will help identify the success of immediately loaded dental implants for orofacial cleft patients and bring the same to regular clinical practice. Dental implants are a fixed treatment option that represent better functionality and aesthetics over conventional alternatives. Immediate loading of dental implants will not only prevent loss of the generated bone due to early functional stimulation but will also provide immediate aesthetic improvement, leading to an enhanced level of self-confidence of the patients. In cumulation, this will help increase patient’s and dentist’s acceptability of the treatment along with substantially reducing the treatment time and costs for such patients who have already undergone prolonged treatments since a young age.

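### Eligibility admits only cleft sites that are grafted a second time, but the objective, aim and scope claim an answer for orofacial cleft patients in general

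*Protocol article*

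**What the plan says.** Three sections of the protocol article fix who receives a study implant.

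- **Inclusion Criteria:** patients must "have undergone secondary alveolar bone grafting (SABG) between 9 and 12 years of age".
- **Exclusion Criteria:** the list removes those who "have a syndromic cleft, do not require tertiary bone grafting, are unable to maintain oral hygiene".
- **Operative Assessment:** screening uses radiographs and "bone mapping to determine the need for tertiary grafting". It continues: "Prior to tertiary grafting, all patients will have the Oral Hygiene Index-Simplified (OHI-S) recorded". The graft is autologous, from the symphysis or the iliac crest, and a CBCT "will be recorded 3-6 months after grafting to evaluate the integration of the grafted bone and plan implant placement".

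Three other places state what the trial is for.

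- **Abstract, Objective:** "determining the treatment outcome of immediately loaded dental implants in patients with a nonsyndromic orofacial cleft".
- **Aim:** to "evaluate the clinical and radiographic success of immediately loaded dental implants in patients with an orofacial cleft".
- **Scope:** "This study will help identify the success of immediately loaded dental implants for orofacial cleft patients and bring the same to regular clinical practice".

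The Limitations section names the small sample and the absence of a control group, and nothing about grafting status.

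**The concern.** The eligibility criteria and the stated question describe different sets of patients. The question is put for people with an orofacial cleft, limited at most to nonsyndromic cases. The criteria admit only those whose childhood graft site has to be grafted again.

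Most trials have an aim broader than their eligibility list, and that alone would not merit comment. This criterion differs because it selects on the bone at the implant site. The outcomes are implant success and marginal bone level, and the condition of that bone bears directly on both. Patients whose SABG was sufficient are an obvious group to whom a general statement about cleft patients would be applied, and the trial will hold no data on them.

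At stake is the reach of the conclusion. A success rate observed in freshly re-grafted sites could be reported, and carried into routine use, as the rate for cleft patients at large.

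**Working it through.** The point rests on reading sections against each other, not on a calculation.

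**Step 1: who can enter.** The Inclusion Criteria require SABG at 9 to 12 years. The Exclusion Criteria remove anyone not needing a tertiary graft. Together they leave patients who had SABG and now need the site grafted again.

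**Step 2: does the treatment pathway agree?** Yes. Operative Assessment screens for the need for a tertiary graft, refers to all patients when it places the hygiene index before that graft, and plans the implant from imaging of the grafted bone. It describes no route to implant placement without a tertiary graft. The Surgical Assessment part of the record sheet also covers tertiary grafting and implant placement together. The literal reading of the exclusion is therefore the one the protocol operates.

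**Step 3: what is claimed.**

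| Section | Population named | Restricted to tertiary-grafted sites? |
|---|---|---|
| Abstract, Objective | Nonsyndromic orofacial cleft | No |
| Aim | Orofacial cleft | No |
| Results | Nonsyndromic alveolar cleft | No |
| Scope | Orofacial cleft patients, with a view to routine use | No |
| Abstract, Conclusions | Sites with compromised bone, as found in cleft patients | Not explicitly; narrower than the Aim |
| Limitations | Not addressed | No |

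In the text at hand, tertiary grafting is named only under Exclusion Criteria, Operative Assessment and Surgical Assessment. Figure 1 and the record sheet itself are not shown. Someone who reads only the abstract, Aim, Scope or Limitations does not learn of the restriction.

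**Step 4: size.** By the criteria as written, 30 of 30 planned implants (100%) are in tertiary-grafted sites and 0 of 30 in sites where SABG alone sufficed. The document does not give the proportion of cleft patients, or of patients with SABG, who need no second graft. The size of the uncovered group cannot be computed.

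**Step 5: does the planned sample size depend on this?** The stated inputs are p = 0.95, margin d = 0.08 and 95% confidence. The usual precision formula gives n = 1.96² × 0.95 × 0.05 / 0.08² = 28.5, against the stated 28. Allowing for 5% loss, 28 / 0.95 = 29.5, so 30 as stated. Nothing in this formula changes if the claim is narrowed.

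**The case against.** The strongest reply is that the design is coherent and open. The exclusion and the pathway agree, and the Discussion gives a reason for placing implants in grafted bone after about 3 months of healing. A one-line aim need not repeat each criterion: the Aim and Scope also omit the limits on age, systemic disease, smoking and bruxism. On that view this is a matter of wording in discussion text.

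Much of this stands. There is no contradiction between criterion and pathway, and the restriction can be found by anyone who reads the Methods. What does not follow is that grafting status is just one more eligibility limit. It defines the bone into which the implant is placed, and the Limitations section, where a reader would look for such a boundary, is silent.

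Four stronger inferences are tempting, and the document does not support them.

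- **The exclusion is an inverted negative and the opposite group was meant.** The wording is awkward, but Operative Assessment follows the literal reading, so this is speculation.
- **The success estimate is biased.** For the patients enrolled it is not biased by this criterion; the question is to whom it extends.
- **The comparison with published rates is invalid.** The 95% in Sample Size Calculation serves only to set precision, and the 95.8% to 98.6% in the Discussion is background. No formal comparison with either is planned.
- **The abstract's Conclusions overreach as plainly as the Scope does.** They speak of feasibility in compromised bone, which fits a re-grafted population fairly well, so they are weak evidence for the point.

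**Conclusion.** The point holds as a mismatch between the enrolled population and the population claimed. As written, every study implant is placed in a tertiary-grafted cleft site, while the abstract's Objective, the Aim and the Scope speak for orofacial cleft patients generally and the Limitations do not disclose the difference. The trial can answer its question for nonsyndromic patients with prior SABG who need a tertiary graft. It provides no data on patients whose SABG left adequate bone.

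This rests on two readings: that the exclusion means what it says, and that the reference to all patients in Operative Assessment is literal. Each supports the other. The proportion of patients outside the claim is unknown, and any percentage would be a guess. The point should be corrected because it changes what the trial may conclude, although it affects neither the conduct of the trial nor its planned analysis.

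**What to change.** Reconcile the abstract's Objective, the Aim, the Exclusion Criteria, Operative Assessment and the Scope so that they describe the same patients.

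- In the objective, aim, conclusion and scope, state the population as immediately loaded implants in tertiary-grafted alveolar cleft sites of nonsyndromic patients with prior SABG.
- In the Limitations, add that the results do not cover patients who need no tertiary graft.

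The cost is a narrower claim and some rewording. Enrolment, procedures, sample size and analysis stay as they are, and no clinical rule has to be changed.
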